## Materials and methods

Study design* *

This cross-sectional study was carried out in the Central Laboratory Department of Pathology at Acharya Vinoba Bhave Rural Hospital, affiliated with Datta Meghe Institute of Higher Education and Research (Deemed to be a University), located in Sawangi, Wardha, Maharashtra, India. The study commenced following the receipt of participants' consent and has been approved by the Institutional Ethics Committee of Datta Meghe Institute of Higher Education and Research (approval number: DMIHER (DU)/IEC/2024/157). It was also registered with the Clinical Trials Registry of India (CTRI/2024/04/066473) (Appendices). A minimum of 314 eligible participants were involved, and the study spanned one year to ensure comprehensive data collection.

Participants

Patients of Indian origin aged 11-65 years diagnosed with anemia will be included. Exclusion criteria include patients diagnosed with leukemia, lymphoma, or other blood disorders as well as those under 11 or over 65 years of age. Patients with chronic kidney disease and liver disease will be excluded as these diseases affect the production of RBS and the indices of erythropoiesis. Patients who are on chronic medications which are known to alter the morphology of RBCs including chemotherapy will also be excluded. Those patients, who were transfused with blood within the last three months, will be excluded from the study since it may shift their RBC parameters slightly.

Data collection procedure

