The complete analysis dataset will consist of all the anemic patients with no missing values for any parameters in the dataset. The primary variables include MCHC, MCV, RDW, and MCHC. All the data will be summarized for the PBS and automated hematology analyzer results of the anemic patients. Demographic variables will be presented using frequencies and percentages for categorical data and means and standard deviations for continuous data. Outcome variables for continuous data will be analyzed and summarized with maximum, mean, minimum, standard deviation, standard error, and a 95% confidence interval for parametric data. Continuous outcome variables will first be tested for normality using the Kolmogorov-Smirnov test at a 5% significance level (p≤0.05). To compare the results of CBC and PBF methods, data will be evaluated finding the sensitivity, specificity, positive predictive value (PPV), negative predictive value (NPV), and accuracy for both methods. If the data is normally distributed, a paired t-test will compare the means of related groups (CBC group with positive and negative cases). If the data is not normally distributed, the Mann-Whitney test will be used. However, the PBS group with positive and negative cases will be evaluated using the chi-squared test or McNemar's test. This analysis will determine the more effective diagnostic method.

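### A Kolmogorov-Smirnov normality pre-test should not choose the analysis of each red-cell index: its version and target are unstated, and its two branches assume different designs

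*Protocol article*

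**What the plan says.** All of this is in the protocol article, Materials and methods, mostly under Statistical analysis.

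- The variables: "The primary variables include MCHC, MCV, RDW, and MCHC" (MCHC is printed twice).
- The pre-test: "Continuous outcome variables will first be tested for normality using the Kolmogorov-Smirnov test at a 5% significance level".
- If it passes: "If the data is normally distributed, a paired t-test will compare the means of related groups (CBC group with positive and negative cases").
- If it fails: "If the data is not normally distributed, the Mann-Whitney test will be used".
- The summaries promised include "standard deviation, standard error, and a 95% confidence interval for parametric data".
- The numbers available: "A minimum of 314 eligible participants were involved" (Study design), restricted by "The complete analysis dataset will consist of all the anemic patients with no missing values for any parameters in the dataset".

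The article gives no reference mean or SD for the test and does not mention a Lilliefors correction. It does not say whether the test is applied to all patients together, within groups, or to paired differences.

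**The concern.** This is a stated decision rule, not a detail left open. It raises four questions.

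1. **Level.** The ordinary Kolmogorov-Smirnov p-value is valid only against a normal distribution whose mean and SD were fixed beforehand. The Introduction gives usual ranges (MCV 80 to 100 fL, MCHC 32 to 36 g/dL), but these do not supply a mean and SD for anemic patients. If both are estimated from the sample and the ordinary table is still used, the test is far more conservative than 5%.
2. **Target.** The Introduction defines the anemia types by MCV cut-offs. If MCV is tested over all types together, the sample is a mixture of groups that were separated on MCV itself. Its overall shape says little about whether a comparison between groups is valid.
3. **Branches.** A paired t-test needs two measurements per unit, and Mann-Whitney needs two independent groups. Positive and negative cases are different patients. A check of shape would therefore end up choosing the assumed design.
4. **Reporting.** If intervals are given only for indices that pass, the indices may be reported unevenly for no clinical reason.

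At stake is a consistent and interpretable analysis of the indices that the article calls primary.

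**Working it through.** **The plan's own figure.** Sample size section, with z = 1.96, p = 0.286, E = 0.05:

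n = z² × p × (1 − p) / E² = 3.8416 × 0.286 × 0.714 / 0.0025 = 313.8, so 314. The planned number reproduces and is the n used below.

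**Step 1: level of the test.** Let z(i) be the i-th ordered value after subtracting the sample mean and dividing by the sample SD. The statistic is

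D = max over i of { i/n − Φ(z(i)), Φ(z(i)) − (i − 1)/n }.

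At n = 314 the ordinary 5% critical value is 0.0761. The simulated critical value that allows for estimated mean and SD (Lilliefors) is about 0.0507. Applying 0.0761 to 300,000 normal samples gave 46 rejections: 46 / 300,000 = 0.00015, or 0.015%. A separate run gave 2 / 20,000 = 0.01%. The stated level is 5%.

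**Step 2: skew that goes unnoticed.** The article gives no distribution for MCV, MCHC or RDW, so the shapes here are assumptions shown as a range (gamma, n = 314, 4,000 samples per shape).

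| Skewness | Called normal, ordinary table | Called normal, Lilliefors |
|---|---|---|
| 0.5 | about 95% to 96% | 42% |
| 0.75 | 71% | 8% |
| 1.0 | 27% to 28% | 0.2% |
| 1.25 | 4% | about 0% |
| 1.5 | about 0% | about 0% |

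Lognormal shapes agree. With the ordinary table, skewness of about 0.6 is called normal in 90%, 0.95 in 47% and 1.3 in 9%. Complete-case restriction can only lower n. If half remained (n = 157, an assumption), gamma skewness 1.0 would be called normal in 79% and 1.5 in 19%.

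**Step 3: if types are pooled (not stated).** Two groups, each exactly normal with equal SD, were combined at n = 314 and tested with the ordinary table.

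| Gap between means | 30%/70% mix rejected | 50%/50% mix rejected |
|---|---|---|
| 2 SD | 4% | 0.3% |
| 2.5 SD | 37% | 6% |
| 3 SD | 91% | 55% |

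At a fixed gap the answer changes with the mix alone. A three-type MCV example (assumed means 68, 88 and 107 fL, SDs 7, 5 and 6) was rejected in 43% to nearly 100% of samples, depending only on the mix.

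**Step 4: does the pre-test protect anything?** An ordinary t-test at 5% was run on gamma data with skewness 0.5 to 2 and total n = 314, 20,000 samples each. The two-sample version used a first group of 31, 90 or 157; the one-sample version stands for the paired test. Type I error lay between 4.7% and 5.3% throughout.

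**Step 5: the branches.** The analyzer gives each patient one value of each index. The smear, as described under PBS, gives a morphological diagnosis. A comparison of an index between positive and negative cases is therefore between two sets of patients. Mann-Whitney fits that structure; the paired t-test does not. The normality result has no bearing on which structure holds.

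**The case against.** The strongest reply is that much of this is conditional and the harm is small.

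- **Version of the test.** The article neither states nor excludes the Lilliefors correction, and software may apply it. The level is then 5%. This stands: a reader might infer that the plan's test certainly fails to run at 5%, but the article does not settle that. The version could be fixed in an analysis plan that is not shown.
- **Pooling.** A reader might take it as given that all patients are tested together. The wording is open, so Step 3 applies only if that is what is done.
- **Size of the skew missed.** A reader might infer that plainly skewed indices will be called normal. The figures do not support that at n = 314: even the ordinary table rejects about 72% to 73% at gamma skewness 1.0 and 96% at 1.25. Only mild to moderate skew is usually missed.
- **Harm.** The t-test holds its level, so sending a skewed index there does not invalidate it at this n, and an over-conservative pre-test mostly selects a t-test anyway. This stands, and it limits the seriousness. It also removes the reason for having the pre-test. It does not rescue the paired form of the t-test.
- **Intervals.** Reading "standard deviation, standard error, and a 95% confidence interval for parametric data" as withholding intervals from other indices is one plain reading of loose wording. The article does not say outright that they are withheld.
- **Main results.** Sensitivity, specificity, PPV, NPV and accuracy, and the chi-squared or McNemar tests, do not depend on the pre-test. This stands in full.

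**Conclusion.** The point holds in a limited form and is worth correcting, though it is not critical. A normality pre-test is fixed as the rule that selects the analysis of each continuous index, and it should not have that role. Three things hold whichever version of the test is meant: the quantity tested is not defined, the two branches assume different designs, and at about 314 patients the pre-test guards against nothing for skewness up to 2.

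Two further faults are conditional. With the ordinary table and estimated parameters, the level is about 0.01% to 0.015% and skewness up to about 0.75 is missed in most samples. With pooling over types, the result for MCV depends largely on case mix.

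The figures assume n = 314 and gamma, lognormal or normal-mixture shapes, none of which the article provides. The type I error check covers groups of 31 or more with the ordinary t-test; smaller groups and Welch's version were not simulated. The consequence is uneven and partly mis-specified analysis of the indices. No inflated false-positive rate or bias in the accuracy measures has been shown.

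**What to change.** In the Statistical analysis section:

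1. Delete the sentence that makes the Kolmogorov-Smirnov result the first step, and the two conditional sentences that follow from it.
2. Name one independent-groups method in advance for comparing an index between groups of patients, for example Welch's t-test with a 95% CI for the difference, and define the groups.
3. Promise a 95% CI for every index whatever its distribution.
4. If a distribution check is kept, do it within group by Q-Q plot or Lilliefors test, and state that it is descriptive and does not alter the analysis.

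The cost is a few sentences. No new data or patients are needed, and the diagnostic-accuracy analyses stay as they are. The downside is negligible. If a group turns out much smaller than the 31 covered by the check above, a bootstrap interval can be named in advance for that case.

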When an erythrocyte's average size is lower than usual, it is known as microcytic anemia (MCV <80 fL). Generally observed in long-term iron deficiency anemia, a variety of conditions can induce macrocytic anemia, a deficiency of vitamin B12, which is characterized by a mean RBC volume that is more than usual (MCV >100 fL). Normocytic anemia is defined as anemia with a low blood count but an MCV in a typical range of 80-100 fL. It can be caused by hemolytic anemia, dietary deficiencies, or renal failure [9].

An automated hematology analyzer produces a graphical representation known as an RBC histogram. It is a standard part of a complete blood picture, which supplies clues in the diagnosis of various RBC disorders and gives valuable data regarding RBC parameters like red blood cell distribution width (RDW), MCH, and MCV [10,11]. The graphical representation of cell frequencies versus size is called a histogram. A cell's size is displayed on the x-axis, while the overall number of cells is displayed on the y-axis. They provide crucial guidance for diagnosing and managing severe disorders affecting RBC [12]. PBS examination, RBC histograms, and RBC indices are essential tools for accurately diagnosing and classifying anemia [13].

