Both the benefits and drawbacks of their participation will be discussed with the participants. To avoid any misunderstandings, participants will be given written information about the consent before their enrolment. Potential volunteers will be chosen based on their primary complaints such as clinical anemia and family history. The blood sample will be drawn while the individual sits securely and in an aseptic setting. Two milliliters of venous blood will be collected in an ethylenediaminetetraacetic acid (EDTA) tube, gently mixed, and processed using a five-part automated hematology analyzer (Coulter) for complete blood count (CBC) testing and the estimation of RBC indices, including MCV, MCH, MCHC, and RDW. Based on various RBC indices and a histogram, the Beckman counter-analysis report will be examined to diagnose the kind of anemia. Simultaneously, a blood smear will be prepared in a Blue Star slide (75 mm length, 25 mm width, 1.35 mm thickness) from the given blood sample and allowed to dry. After that, staining will be performed using Leishman's stain and Leishman's buffer. The smear will next be examined under a microscope with an oil immersion lens (100×), and the findings will be recorded to make the morphological diagnosis of anemia. One pathologist will independently perform the morphological analysis to ensure accuracy and consistency. The PBS and cell counter methods will be used to collect the data, and the data will be compared and analyzed by using tests like the paired t-test and chi-squared test to draw a conclusion.

CBC

After the blood sample is collected in the EDTA tube, it will be sent to the pathology processing lab. The sample will be aligned in a cassette for processing. Then the cassette will be kept in the Beckman Coulter B1 (UniCel DxH 800). By using the principle of electrical impedance, results will be given by the machine, and this result will be used to analyze CBC and its relation with anemia. Based on various RBC indices and a histogram, the Beckman counter-analysis report will be examined to diagnose the kind of anemia.

PBS

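### On its plain reading, the planned test within the CBC group compares the analyzer's indices across groups formed from those same indices and never uses the smear, so it cannot show which method is better

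*Protocol article*

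**What the plan says.** All places are in the protocol article.

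- **Statistical analysis, variables:** "The primary variables include MCHC, MCV, RDW, and MCHC". MCHC appears twice. MCH, which Data collection procedure lists among the indices to be estimated, does not appear.
- **Statistical analysis, test:** for normally distributed data, a paired t-test is to "compare the means of related groups (CBC group with positive and negative cases"). Otherwise: "If the data is not normally distributed, the Mann-Whitney test will be used". The next sentence gives the PBS group its own split into positive and negative cases, to be analysed by chi-squared or McNemar's test.
- **Statistical analysis, purpose:** the paragraph ends: "This analysis will determine the more effective diagnostic method".
- **Data collection procedure, repeated under CBC:** "Based on various RBC indices and a histogram, the Beckman counter-analysis report will be examined to diagnose the kind of anemia".
- **Introduction, the only numeric class limits:** "When an erythrocyte's average size is lower than usual, it is known as microcytic anemia (MCV <80 fL"); macrocytic anemia is "characterized by a mean RBC volume that is more than usual (MCV >100 fL"); normocytic lies between, at 80-100 fL.
- **Results:** the RBC histogram is to be judged against the smear examination as the traditional method.

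**The concern.** The tested variables are analyzer outputs. If the positive and negative groups are also analyzer outputs, formed from the same indices, the comparison is circular. A difference in mean MCV between patients called microcytic and the others then restates the cut-off. It would appear even if the analyzer's typing had no relation to what the pathologist sees on the slide.

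The article places this test in the paragraph that is to decide which method is more effective. A very small p-value from it could be read as support for the histogram and indices when it carries no information about agreement with the smear.

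The sentence has a second fault. Positive and negative cases are different patients, so a paired t-test does not apply, and the named fallback is an unpaired test. Correcting the pairing alone would leave the circularity in place.

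**Working it through.** **1. The plan's own figure.** The article states no effect size or power for this test. Its sample size does reproduce: n = 1.96² × 0.286 × 0.714 / 0.05² = 313.79, rounded up to 314. N = 314 is used below.

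**2. What enters the test.** Tested variable: MCV, MCHC or RDW from the analyzer. Group label: the CBC type call, made from the indices and histogram. The Introduction describes the histogram as the cell-size distribution and a source of MCV and RDW, so using it does not bring in outside information. The smear result enters neither side.

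**3. One-sided split, by arithmetic.** Let positive mean MCV <80 fL (the Introduction's limit) and negative mean the rest. Every positive lies below 80 and every negative at or above it, so mean(positive) < 80 ≤ mean(negative) for any data. The Mann-Whitney U is 0, its most extreme value. With n₁ positives and n₀ negatives, the normal approximation gives |z| = (n₁n₀/2) / √(n₁n₀(N+1)/12) = √(3n₁n₀/(N+1)).
- n₁ = n₀ = 157: √(3 × 157 × 157 / 315) = 15.3.
- n₁ = 33, n₀ = 281: √(3 × 33 × 281 / 315) = 9.4.
- n₁ = 2, n₀ = 312: √(3 × 2 × 312 / 315) = 2.44, still above 1.96.

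**4. One-sided split, by simulation.** 2,000 runs per scenario, N = 314, MCV normal. The article gives no MCV distribution, so means and SDs are assumptions. No smear data are used.

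| Assumed mean (fL) | Difference, SD 8 | Difference, SD 12 | Rejection at 5%, Welch and Mann-Whitney |
|---|---|---|---|
| 75 | -13.4 | -19.6 | 100% |
| 80 | -12.8 | -19.1 | 100% |
| 85 | -13.5 | -19.6 | 100% |
| 90 | -15.5 | -21.0 | 100% |

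The built-in difference is thus about 13 to 21 fL. As a check, at mean 80 the exact difference for a normal variable is SD × 0.3989 / 0.25 = 1.596 × SD, which is 12.8 for SD 8 and 19.1 for SD 12. Further scenarios at 75±12, 82±12 and 90±10 fL also gave 100%.

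**5. Two-sided split.** Let positive mean MCV <80 or >100 fL and negative mean 80-100 fL. At assumed means of 80, 85 and 95 fL, rejection was again 100%. At 90 fL, midway between the limits, low and high values cancel and the mean difference is about 0. With SD 10, rejection was about 5% (Welch) and 17% (Mann-Whitney); with SD 8 or 12, about 4-6% and 15-20%. Neither rejection nor non-rejection involves the smear.

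**6. Other indices.** For an index correlated with the one that forms the groups, the Welch test rejected in about 5%, 82% and 100% of runs at assumed correlations of size 0, 0.2 and 0.4. The article gives no such correlations and no class limits for RDW or MCHC.

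**7. Grouping by the smear instead.** With a smear label generated independently of MCV, rejection was 4.6% at an assumed 85±12 fL, close to the nominal 5%. Grouping by the reference removes the artefact.

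**The case against.** The strongest reply is that the article never says what positive and negative mean, so circularity is a reading and not a stated fact. Three other readings are possible.

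- *Analyzer values split by smear status.* Results does make the smear the reference, and the sentence before the test concerns sensitivity and specificity. On this reading there is no circularity and the plan is close to the fix below. But the matching phrase for the PBS group suggests that each method is split by its own result, and nothing in the sentence mentions the smear.
- *CBC against smear in the same patients.* The words paired and related point this way, as does the general remark in Data collection procedure. But the article describes only a morphological diagnosis from the smear, with no MCV, MCHC or RDW reading to pair with the analyzer's.
- *Positive meaning anemic.* The analysis set holds only anemic patients, so there would be no negative group.

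An analysis plan not shown here might define the terms. The protocol nevertheless names the groups and the test itself, so the sentence can be judged as it stands.

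A reader might go further and make three inferences that the documents do not support.

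1. *MCV must differ under any split.* This holds only for one-sided splits; the abnormal-versus-normocytic case at 90 fL shows the exception. The MCV limits are also Introduction background, not a stated study rule, and the CBC call uses several indices and the histogram.
2. *RDW and MCHC suffer equally.* That rests on assumed correlations and on their unknown part in the call.
3. *The whole method comparison is a false positive by design.* Sensitivity, specificity, PPV, NPV and accuracy are planned separately to compare the two methods. Table 1 contains those measures plus time and cost, and no index means or p-values. The disputed test feeds none of its cells.

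**Conclusion.** Wrong as written; should be fixed. The groups are undefined, and on the plain reading the test is circular and leaves out the reference method. It therefore cannot contribute to deciding which method is more effective, and an unpaired test would not change that.

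For a one-sided split at the Introduction's MCV limit, the direction of the difference is certain. Rejection at N=314 was 100% in every assumed scenario. For abnormal versus normocytic, rejection ranges from about 5% (Welch, 90±10 fL) to 100% depending on where MCV is centred, and it is uninformative throughout. For RDW and MCHC the size is unknown.

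The conclusion rests on reading positive and negative as the analyzer's calls. The figures rest on assumed normal MCV distributions, except the ordering argument for one-sided splits, which needs none. The planned accuracy measures are not affected.

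**What to change.** In Statistical analysis:

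1. Define positive and negative for each anemia type (microcytic, normocytic, macrocytic) by the type assigned on the smear.
2. Replace the comparison within the CBC group by a comparison of MCV, MCH, MCHC and RDW between smear-assigned types. Use an unpaired test: Welch t or ANOVA, or Mann-Whitney or Kruskal-Wallis where normality fails. Give differences with 95% CIs.
3. State that index means by CBC-assigned type are descriptive and carry no p-value.

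The cost is a few lines of text, plus agreement on the definition for each type before the wording is settled. No new data are needed, because the indices and the smear diagnosis are already to be recorded for each patient. The downside is that p-values will be less extreme.

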## Results

This study therefore seeks to determine whether an RBC histogram can diagnose the three types of anemia, microcytic, macrocytic, and normocytic [15], with reference to the traditional method of diagnosing the condition using the PBS examination. This study will determine the efficiency of RBC histogram analysis by comparing the diagnostic findings with that of PBS examination which will be used. Thus, the use of this approach will offer the researcher an understanding of how efficient RBC histogram analysis is as compared to the PBS examination in the identification of diverse types of anemia. Better results in diagnostic capabilities are expected, with RBC histograms likely providing more precise and quantifiable data on RBC indices. Implementing RBC histogram analysis in routine clinical practice is expected to enhance diagnostic processes for anemia, leading to a more effective and timelier patient treatment.

Table 1 shows the metric table to compare the RBC histogram and PBS.

**Table 1 TAB1:** Metric table to compare the RBC histogram and PBS RBC: red blood cell; PBS: peripheral blood smear; PPV: positive predictive value; NPV: negative predictive value

Metric	RBC histogram	PBS
Sensitivity		
Specificity		
PPV		
NPV		
Diagnostic efficiency (overall accuracy)		
Time per sample		
Cost per test		

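### The named tests are tied to single-method groups, so the CBC-versus-PBS comparison on paired samples is only descriptive and has no valid paired test

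*Protocol article*

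**What the plan says.** All references are to the Protocol article.

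- **Pairing.** In Data collection procedure, one EDTA tube per patient goes to the analyser and the smear comes from that same sample: "Simultaneously, a blood smear will be prepared in a Blue Star slide".
- **Aim.** Results names three anemia types (microcytic, macrocytic, normocytic) and states: "This study will determine the efficiency of RBC histogram analysis by comparing the diagnostic findings with that of PBS examination which will be used".
- **Descriptive comparison.** Statistical analysis says: "To compare the results of CBC and PBF methods, data will be evaluated finding the sensitivity, specificity, positive predictive value (PPV), negative predictive value (NPV"), together with accuracy. No test or interval for a difference between methods is attached.
- **Test for CBC.** With normal data, "a paired t-test will compare the means of related groups (CBC group with positive and negative cases"). Otherwise: "If the data is not normally distributed, the Mann-Whitney test will be used".
- **Test for PBS.** "the PBS group with positive and negative cases will be evaluated using the chi-squared test or McNemar's test", with no rule for choosing between the two.
- **Conclusion drawn.** The section closes by saying that this analysis will settle which diagnostic method is the more effective.
- **Elsewhere.** Data collection procedure says that the data from both methods will be "compared and analyzed by using tests like the paired t-test and chi-squared test to draw a conclusion". McNemar's test is not mentioned there.

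**The concern.** The study asks how the analyser's classification relates to the smear's classification of the same patient. That calls for a paired analysis of categories. The named tests instead look inside one method at a time, and two of them (chi-squared and Mann-Whitney) are tests for independent samples.

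Someone following the text would have to run a test that is not defined for the data, or improvise. Two improvised uses of chi-squared are likely, and each has a cost. Comparing the two methods' positive rates as independent samples uses too large a variance and can miss a systematic difference. Applying chi-squared to the cross-table tests only whether the methods are associated, which two methods reading the same blood will almost always be. With chi-squared and McNemar offered as alternatives, the conclusion could turn on a choice that the plan does not make.

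**Working it through.** **1. The plan's own figure.** Sample size, from the worked line: 1.96² × 0.286 × 0.714 / 0.05² = 313.79, rounded up to 314. It reproduces. It is a precision calculation for a prevalence and says nothing about power for a paired comparison. N = 314 is used below.

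**2. Each named test against the data structure.**

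| Named test | Where the plan applies it | What it needs | Result |
|---|---|---|---|
| Paired t-test | Positive v negative cases, CBC group | Two measurements on each patient | Undefined: the two sets are different patients |
| Mann-Whitney | Fallback for the paired t-test | Independent samples | Ignores pairing if used between methods |
| Chi-squared | PBS group | Independent observations | Ignores pairing if used on the two methods' rates |
| McNemar | PBS group | Two classifications of each patient | Cannot be run within one method; valid on the CBC-by-PBS table |

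**3. Illustration of the size.** The documents give no discordance rates, so the cell counts are assumed. Take one type, yes or no, N = 314: both methods positive 150, CBC only 25, PBS only 9, neither 130.

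- Positive rates: CBC 175/314 = 55.7%; PBS 159/314 = 50.6%; difference 16/314 = 5.1 points.
- Unpaired chi-squared: pooled rate 334/628 = 0.532; variance 0.532 × 0.468 × 2/314 = 0.001586; (16/314)² / 0.001586 = 1.64, **p = 0.20**.
- Exact McNemar, 25 v 9 among 34 discordant pairs: **p = 0.009**.
- Chi-squared on the cross-table: 314 × (150×130 − 25×9)² / (175×139×159×155) = 194.6, p = 3 × 10⁻⁴⁴.
- Agreement: (150 + 130)/314 = 0.892. Expected: (175×159 + 139×155)/314² = 0.501. Kappa = (0.892 − 0.501)/(1 − 0.501) = 0.78.

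**4. Dependence on the assumed counts** (150 both positive, N = 314):

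| CBC only / PBS only | Unpaired chi-squared p | Exact McNemar p | Same conclusion at 5%? |
|---|---|---|---|
| 25 / 9 | 0.20 | 0.009 | No |
| 20 / 14 | 0.63 | 0.39 | Yes |
| 40 / 10 | 0.016 | 0.00002 | Yes |

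For 20/14 the association chi-squared is 192.6 and kappa is again 0.78, almost as for 25/9. Neither figure tells a systematic shift from a balanced one; McNemar does.

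**5. Simulation** (200,000 replicates, N = 314, both positive in 60%, nominal 5%, uncorrected statistics).

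- No true difference, discordance 5% to 30%: McNemar rejects in 4.9–5.1%, unpaired chi-squared in 0.0–2.9%, association chi-squared in 93–100%.
- True difference 5 points, discordance 10%: power 83% for McNemar, 8% for unpaired chi-squared.
- True difference 7 points, discordance 20%: 80% v 47%.

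**6. The Mann-Whitney fallback,** if applied to paired continuous values (2,000 replicates, assumed correlations 0.5 and 0.8): rejection under no shift is 0.3% and 0.0%, against about 5% for the Wilcoxon signed-rank test. At a shift of 0.15 SD, power is 43% and 41%, against 75% and 99%.

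**The case against.** A reader might infer that the plan never brings the two methods together. The text does not support that. Statistical analysis lists accuracy measures for the purpose of comparing the methods, and Results evaluates the histogram with reference to PBS. Histogram sensitivity and specificity against PBS require the cross-table. The comparison is planned descriptively; what it lacks is a correctly attached paired test.

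A reader might also infer that chi-squared is fixed as the deciding test. Data collection procedure only gives examples of tests, and the governing section names McNemar as well. McNemar would be valid on the CBC-by-PBS table. Its restriction to two categories is not a fault here, because the section speaks of positive and negative cases, which fits an analysis type by type.

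Nor do the documents support saying that the conclusion will reverse. Neither improvised use of chi-squared is written down, and the reversal depends on the assumed counts: with 20/14 and 40/10 the two tests agree. The unpaired test errs towards lost power, not towards false claims of a difference. The association test answers another question, so its p-value is not an opposite answer.

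These objections limit the point but do not remove it. The section still attaches each test to a single-method group, treats a paired and an unpaired test as interchangeable, and rests the choice of method on the outcome. That is stated in the text, not left to a later analysis plan.

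**Conclusion.** The point holds in this form: the inferential tests are attached to single-method groups although the classifications are paired, and the CBC-versus-PBS comparison has only descriptive accuracy measures and no valid paired test. Following the text gives a test that is undefined or that ignores the pairing.

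The structural finding needs no assumption beyond the single shared sample. The size does rest on assumption. Under the illustrative counts of 25 and 9, the choice between unpaired chi-squared and McNemar moves p from 0.20 to 0.009; under other counts it changes nothing. In the simulated settings the loss of power ranges from 33 points (80% v 47%) to 75 points (83% v 8%).

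A paired test would not by itself show which method is better. PBS is the comparator in Results and is called the gold standard in Discussion, yet Table 1 also gives it a sensitivity and specificity of its own. Kappa and marginal-homogeneity tests measure agreement and systematic shift, not accuracy.

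Severity: should be fixed. The descriptive measures do not depend on the test choice, and a suitable test is already named.

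**What to change.** In Data collection procedure and Statistical analysis:

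1. Cross-tabulate CBC/histogram type by PBS type in the same patients.
2. Report overall agreement and Cohen's kappa with 95% confidence intervals.
3. Use exact McNemar per anemia type on that table, with Stuart-Maxwell or Bowker as the global test across the three types.
4. Delete chi-squared, and the within-CBC-group paired t-test with its Mann-Whitney fallback, as tests of the method comparison.
5. Report histogram sensitivity and specificity with PBS as the reference.
6. Restate the conclusion as agreement with PBS rather than as a finding of which method is more effective.

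The cost is analysis wording only: no new patients, samples or procedures, and standard software.
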